### Secondary Efficacy Endpoints

For each secondary efficacy endpoint, descriptive statistics will be presented at baseline, 12 weeks, and 24 weeks. The change from baseline to 12 weeks or 24 weeks will be analyzed using mixed-effects models or GEE to account explicitly for clustering effects. Patient-level covariates will be included as fixed effects, and inter-center variability as random effects.

### Exploratory Endpoints

For each exploratory endpoint, descriptive statistics will be presented at baseline, 12 weeks, and 24 weeks. The change from baseline to 12 weeks or 24 weeks will be analyzed using mixed-effects models or GEE to account explicitly for clustering effects. Patient-level covariates will be included as fixed effects, and inter-center variability as random effects. Multiple comparisons within exploratory endpoints will be adjusted using the Benjamini–Hochberg false discovery rate method, with statistical significance defined at q ≤ 0.05.

1. **Safety Endpoints**

### Vital Signs

For vital signs, descriptive statistics will be presented at baseline, 6 weeks, 12 weeks, 18 weeks, and 24 weeks. The change from baseline at 24 weeks or at 6, 12, and 18 weeks will be analyzed using mixed-effects models or GEE to account explicitly for clustering effects. Patient-level covariates will be included as fixed effects, and inter-center variability as random effects.

### Laboratory Tests

For laboratory tests, descriptive statistics will be presented at baseline, 6 weeks, 12 weeks, 18 weeks, and 24 weeks. The change from baseline at 24 weeks or at 6, 12, and 18 weeks will be analyzed using mixed-effects models or GEE to account explicitly for clustering effects. Patient-level covariates will be included as fixed effects, and inter-center variability as random effects.

Additionally, the frequency and percentage of normal (Normal or NCS) and clinically significant abnormal (CS) changes will be summarized. Detailed information on subjects with clinically significant abnormal (CS) items will also be listed.

1. **Subgroup Analysis**

If a subgroup analysis based on the characteristics of the subjects is required, each item can be analyzed similarly to the efficacy and safety evaluation variables (e.g., analysis of primary efficacy evaluation results by gender etc.)

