**List of Abbreviations**

| ALT | Alanine Aminotransferase |
| --- | --- |
| ASCVD | Atherosclerotic cardiovascular disease |
| AST | Aspartate Aminotransferase |
| BMI | Body Mass Index |
| CFR | Code of Federal Regulations |
| CS | Clinically Significant |
| DPP-4 | dipeptidyl peptidase 4 |
| eCRF | electronic Case Report Form |
| EDC | Electronic Data Capture |
| FPG | Fasting Plasma Glucose |
| GCP | Good Clinical Practice |
| GLP-1 | Glucagon-like Peptide-1 |
| γ-GTP | Gamma glutamyl transferase |
| HbA1c | Hemoglobin A_1c_ |
| HDL-C | High Density Lipoprotein Cholesterol |
| ICH | International Council for Harmonisation |
| IEC | Independent Ethics Committee |
| IRB | Institutional Review Board |
| LDL-C | Low Density Lipoprotein Cholesterol |
| NCS | Not Clinically Significant |
| SE | Standard Error |
| SOP | Standard Operating Procedures |
| TC | Total Cholesterol |
| TG | Triglyceride |
| UACR | Urine Albumin to Creatinine Ratio |
| UGCR | Urine Glucose to Creatinine Ratio |
|  |  |
|  |  |
|  |  |

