## Exclusion Criteria

Individuals who meet any of the following exclusion criteria will be excluded from this clinical study

1. Individuals with diabetes other than Type 2 Diabetes (e.g., Type 1 Diabetes, Diabetic Ketoacidosis, Gestational Diabetes, etc.)
2. Individuals who fall under the contraindications for administration according to the approved conditions of Envlo Tab. or Envlomet SR Tab.

- Patients who have hypersensitivity or a history of hypersensitivity to any component of Envlo Tab. or Envlomet SR Tab.
- Individuals with an estimated Glomerular Filtration Rate (eGFR) less than 30 mL/min/1.73m²
- Patients with renal impairment with an eGFR less than 60 mL/min/1.73m², end-stage renal disease, or those on dialysis
- Individuals with moderate to severe hepatic impairment (AST or ALT > 3 times the upper limit of normal, Total Bilirubin > 2 times the upper limit of normal, hepatitis, or liver failure)
- Individuals classified as class III or IV according to the New York Heart Association (NYHA) classification

1. Patients who have undergone treatment with obesity medications or weight loss drugs, or other treatments (surgery, diet, etc.) leading to unstable weight within 3 months prior to the enrollment date
2. Individuals with mental incapacity
3. Pregnant or breast-feeding women
4. Individuals participating in another clinical trial and receiving investigational drugs or investigational medical devices
5. Individuals who have prior experience using the Well Check application before study enrollment
6. Individuals deemed unsuitable for participation in this clinical study based on the judgment of the investigator (responsible physician)

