**[Test Group]**

For the test group, the basic usage of the 'Well Check' smartphone application is recommended as follows. Within the 'Well Check' app, investigators and subjects are encouraged to freely use the features considering the subject's medical condition. If self-recording for chronic disease management such as [Blood Glucose], [Blood Pressure], [Weight], [Medication Records], or regular completion of [Health Education] in 'Well Check' is insufficient, the investigator can encourage self-management and education completion via the messaging feature of 'Well Check.'

1. Visit 1 (Baseline, Day 0)

- Subject: Complete [Basic Questionnaire], [Health Checkup Results], and set [Medication Alarm] in the 'Well Check' application.
- Investigator (Responsible Physician): Enter [Blood Test Results], evaluate [ASCVD risk], and use the linked subject's medical history, lifestyle, and symptoms for consultation in the 'Well Check Doctor Web.'
- See Appendix 6. Provide and guide the “Attachment 6. Well Check User Guide” pamphlet.

1. Visit 2 (Follow-up Visit, 6 weeks) to Visit 5 (Close-out Visit, 24 weeks)

- Subject: Enter [Pre-visit Questionnaire] in the 'Well Check' application during visits.
- Investigator (Responsible Physician): Review and analyze the patient’s self-records (questionnaire, blood glucose, blood pressure, weight, medication records) and recent symptoms and lifestyle (alcohol/smoking/exercise) feedback in the 'Well Check Doctor Web.' Enter [Blood Test Results] (if tested), evaluate [ASCVD risk], and use it during consultations

1. During the Study Period (Visit 1 to Visit 5)

- Subject: Record [Blood Glucose] (at least once daily), [Medication Records] (when taking medication), [Blood Pressure] and [Weight] (at least once weekly) in the 'Well Check' application. Complete [Primary Doctor Messages] education (twice weekly) and use [Health Education].
- Investigator (Responsible Physician): Monitor cautionary patients* in 'Well Check Doctor Web' (once weekly) and send encouragement messages to those who do not measure blood glucose (once monthly)

**An alert is sent to 'Well Check Doctor Web' if the blood glucose level is below 54 mg/dL or above 200 mg/dL*

- Automatic dispatch of subject educational materials (twice weekly)

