Laboratory tests are collected based on standard clinical procedures in a real-world clinical setting. If there are HbA1c results within 4 weeks prior to Visit 1 (Baseline, Day 0) or other test results collected within 3 months, these results can be used as substitutes for the laboratory tests at Visit 1 (Baseline, Day 0).

Cardiovascular disease complication risk (Atherosclerotic Cardiovascular Disease risk, ASCVD risk) will be assessed using the ASCVD 2013 Risk Calculator from AHA/ACC. Analysis will be conducted after the study is completed based on information collected in the eCRF (gender, age, systolic blood pressure, total cholesterol, HDL-C, hypertension medication use, diabetes diagnosis, and smoking status). For the test group, the automatic calculation feature within the Well Check app allows investigators (responsible physicians) to input cholesterol and blood pressure values for use during patient consultations.

Examples of Laboratory Test Items to be Collected:

| Main Laboratory Tests | HbA1c, FPG |
| --- | --- |
| Other Laboratory Tests | Total Cholesterol, HDL-C, LDL-C, Triglyceride, ALT, AST, γ-GTP, Creatinine, e GFR, UACR, UGCR |

1. **Well Check Usage Satisfaction Survey**

The satisfaction survey on the usage experience of 'Well Check' by both medical staff and subjects will be conducted in writing during Visit 5 (Close-out Visit, Week 24).

The survey consists of 10 questions and 5 scales designed to evaluate satisfaction with the use of the 'Well Check' application. It is a general survey aimed at assessing the effectiveness of chronic disease management and improvement in work efficiency due to the application usage, rather than targeting any specific disease group.

The 10 questions of Medical Staff Satisfaction Survey aim to assess the effectiveness of managing patients with chronic diseases and the improvement in work efficiency due to the use of the application. The 5-point scale consists of 1) Strongly Disagree 2) Disagree 3) Neutral 4) Agree 5) Strongly Agree

The 10 questions of Subject Satisfaction Survey aim to assess the satisfaction with the relationship with medical staff and the helpfulness of the treatment process experience due to the use of the application. The 5-point scale consists of 1) Strongly Disagree 2) Disagree 3) Neutral 4) Agree 5) Strongly Agree

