## Randomization

Due to the practical constraints of primary care settings, where it is challenging to manage test group and control groups separately within the same institution, cluster randomization will be used. Institutions will be randomized as either the test group [institutions managing subjects with the 'Well Check' app in conjunction with the investigator (responsible physician)] or the control group (institutions where subjects use the 'Well Check' app for self-management).

For cluster randomization, participating primary medical institutions will be divided into small groups based on basic characteristics [age of the treating physician (45 years and older, or younger), region (metropolitan, non-metropolitan)]. Within these small groups, the test group and control group will be randomly assigned in a 1:1 ratio using the cluster randomization method.

To ensure strict randomization, an independent person not related to this clinical study will prepare the randomization list using the Proc PLAN procedure of SAS (Ver. 9.4 or higher, SAS Institute, Cary, NC, USA). The generated randomization list will be provided to the IWRS (interactive web response system) developer. The randomization number will be verified through IWRS.

After obtaining written consent for participation in this clinical study, the subject's screening test results will be evaluated. Only those who meet the inclusion criteria and do not fall under the exclusion criteria will be assigned a Randomization Enrollment Number.

The randomization enrollment number will be given out as “AAA-RXX-YYY” and means the following.

- “AAA”: Institution identification number
- “R”: Cluster Randomization
- “XX”: Stratification identifiers [age of the treating physician (45 years and older, or younger), region (metropolitan, non-metropolitan)]

- “YYY”: Order of randomly assigned subjects

|  | Metropolitan (X1) | Non-metropolitan (X2) |
| --- | --- | --- |
| 45 years and older (1X) | 11 | 12 |
| 45 years or younger (2X) | 21 | 22 |

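### The laboratory safety table counts abnormal values labelled not clinically significant as normal, so its percentages mix true abnormality with a label that has no stated criterion

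*Protocol*

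**What the plan says.** Section 7.2, Laboratory Tests (under Safety Endpoints), plans two kinds of output.

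- **Values.** Descriptive statistics are given at baseline and weeks 6, 12, 18 and 24. Change from baseline "will be analyzed using mixed-effects models or GEE to account explicitly for clustering effects".
- **Categories.** As an addition, "the frequency and percentage of normal (Normal or NCS) and clinically significant abnormal (CS) changes will be summarized". The section continues: "Detailed information on subjects with clinically significant abnormal (CS) items will also be listed".

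The List of Abbreviations expands NCS as "Not Clinically Significant" and goes no further. No threshold, reference range or grader is named there, in the schedule of data collection, or in section 4.4 (Information and Items Collected).

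On where the results come from, section 4.4 says: "Laboratory tests are collected based on standard clinical procedures in a real-world clinical setting". Section 4.3 (Visit Schedule) adds investigator assessments as a data source. No central laboratory or blinded assessment is described.

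On allocation, section 4.5 says: "Institutions will be randomized as either the test group" or the control group. In the test group, section 4.4 asks the physician to "Review and analyze the patient’s self-records" in the physician web. In the control group it tells the physician not to use the app data. The physician therefore knows the arm in both groups.

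**The concern.** A laboratory result can fall into three states: within range, out of range but judged NCS, and out of range and judged CS. The planned table has two rows and places the middle state with normal. A reader of the table cannot see how many patients had out-of-range results, and the listing does not recover them because it is limited to CS items.

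What separates the two rows is then a judgement without a stated rule. If the clinic physician makes it, each physician's threshold for CS falls entirely into one arm, because clinics are the unit of allocation. Had patients been randomised within clinics, such habits would largely cancel.

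This table is the only categorical laboratory safety result in the protocol. Section 7.1 names only laboratory tests, vital signs and physical examination as safety endpoints. A patient-level laboratory signal therefore depends heavily on it, and a difference in labelling could create or hide a difference between arms.

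**Working it through.** The protocol gives no figure for this point, so there is nothing to reproduce. The check is of the mechanism and its plausible size.

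**Inputs from the protocol.** 24 institutions allocated 1:1 give about 12 per arm (Synopsis; section 4.5). With 20 patients per clinic (section 3.2), 12 × 20 = 240 per arm are enrolled; after 20% dropout about 16 remain per clinic.

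**Assumed inputs** (no source in the protocol). The share of patients with an out-of-range value is π. The share of those values labelled CS is q.

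**Formula.** CS% = π × q. The row called normal is 1 − π × q, which includes the abnormal-NCS share π × (1 − q).

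**Case 1: labelling varies between clinics but not by arm.** Take π = 15% in both arms and q uniform from 0.2 to 0.8 across clinics.

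- Mean CS% = 0.15 × 0.5 = 7.5%.
- SD of q between clinics = 0.6/√12 = 0.173.
- SD of the arm difference in mean q = 0.173 × √(2/12) = 0.071.
- SD of the arm difference in CS% from labelling alone = 0.15 × 0.071 = 1.1 points, a 95% range of about ±2.1 points. A simulation of 20,000 draws gave −2.1 to +2.0 points, and an arm ratio of 0.76 to 1.32.
- SD from ordinary patient sampling = √(2 × 0.075 × 0.925/240) = 2.4 points.
- Combined SD = √(2.4² + 1.1²) = about 2.6 points, roughly 9% more than sampling error alone.

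A second set of assumptions used 12 clinics of 16 patients per arm, mean q = 30%, and a correlation of labelling within clinics from 0 to 0.3. The SD of the arm difference in CS% was:

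| True abnormal rate | No clinic effect | Correlation 0.3 |
| --- | --- | --- |
| 10% | 1.7 points | 2.0 points |
| 20% | 2.4 points | 3.1 points |
| 30% | 2.9 points | 4.2 points |

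In all these cases the difference is centred on zero: the label adds noise, not bias.

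**Case 2: labelling differs by arm, with equal true abnormality.**

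| π in both arms | q test | q control | CS% test | CS% control |
| --- | --- | --- | --- | --- |
| 15% | 60% | 40% | 9.0% | 6.0% |
| 10% | 40% | 20% | 4.0% | 2.0% |
| 20% | 40% | 20% | 8.0% | 4.0% |
| 30% | 40% | 20% | 12.0% | 6.0% |

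The ratio of CS percentages equals the ratio of labelling rates (1.5 or 2.0), so this restates the assumption. It shows that a labelling difference passes straight into the table. It does not show that such a difference exists.

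**Do the value-based analyses fill the gap?** One patient among 240 moves an arm mean by 1/240, or 0.4%, of that patient's own change. A few marked abnormalities are therefore almost invisible in a mean change. The descriptive statistics include the maximum (section 7.2, General Principles), which shows that an extreme value occurred but not how many patients became abnormal.

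**The case against.** The strongest reply is that laboratory safety does not rest on this table. The same section plans descriptive statistics and cluster-adjusted models of the values, neither of which uses the label. Changes in AST, ALT, γ-GTP and eGFR are also exploratory endpoints with cluster-adjusted models. The categorical table is an addition, to be summarised without a planned between-arm test. This stands, and it keeps the point minor. It does not answer how many individuals became abnormal.

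Second, the protocol does not say who assigns CS or NCS. That the clinic physician does so is an inference from the reliance on routine care and investigator assessments. This also stands.

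Third, every rate in the calculation is assumed, and under labelling unrelated to arm the extra noise is small beside sampling error. The more intensive review asked of test-group physicians does not show that they label more values CS. Both remarks are correct.

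Fourth, grading criteria and table layout often belong in a statistical analysis plan, which is not at hand, and the section's reference to changes may mean that some comparison with baseline is intended. This holds for criteria and layout. It does not cover the pooling, which the protocol itself fixes.

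**Conclusion.** The point holds as a minor one. The protocol fixes a two-row table in which abnormal-NCS values count as normal, lists CS items only, and gives the label no criterion or grader. With clinics as the unit of allocation and physicians who know the arm, the CS percentage mixes true abnormality with labelling practice.

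A reader might infer that the table compares labelling habits instead of abnormalities. The documents do not support that: CS% is a product of both, so true differences still show through. Nor do they support a claim of bias. Labelling unrelated to arm averages over about 12 clinics per arm and adds an SD of about 1.1 points to about 2.4 points of sampling error, under the 15% and 20%-to-80% assumptions. Bias requires labelling that differs by arm, which is possible but not shown. Nor are abnormal values lost from the safety evaluation, since the values themselves are summarised and modelled.

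**What to change.** In section 7.2, Laboratory Tests:

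1. Report three rows by arm and visit: Normal, abnormal-NCS and abnormal-CS.
2. Add a shift table from baseline by arm, with each result classed by program as below, within or above the laboratory reference range, in the same way in both arms. Give the number of patients with both results as the denominator, because tests are done only as routine care requires.
3. Keep the CS call for the listing, and state who makes it and on what basis.

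Limits such as "AST or ALT > 3 times the upper limit of normal" and the eGFR limits in section 3.4 are eligibility criteria. They may serve as optional tabulation flags, but nothing in the protocol makes them on-study clinical rules, and this change should not turn them into such rules.

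The cost is table programming and recording each clinic's laboratory reference ranges once in the eCRF. The laboratory values are already collected, and no visit or test is added.

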# Ethical Considerations and Administrative Procedures

## Ethics Committee/Institutional Review Board (IRB)

This clinical study must receive prior approval from the IRB for the protocol and all related matters before initiation. The IRB will review the ethical and medical validity of the study and provide written documentation of their decision to the investigator and the study sponsor. Any amendments or changes to the protocol during the study must be submitted to and approved by the IRB.

## Ethical Considerations

This clinical study will be conducted in accordance with the ethical principles based on the Declaration of Helsinki (Ethical Principles for Medical Research Involving Human Subjects) and in compliance with the Bioethics and Safety Act and related regulations, prioritizing the rights, safety, and welfare of the study subjects.

## Quality Assurance and Audit

The sponsor will implement quality assurance and quality control of clinical study data in accordance with the sponsor's standard operating procedures (SOPs) to ensure that the study is conducted, data are generated, recorded, and reported in compliance with the protocol, the Bioethics and Safety Act, and related regulations.

The auditor will conduct audits following the procedures below.

1. Audits will be conducted according to the safety regulations of pharmaceuticals [Appendix 4] and the Good Clinical Practice (GCP) standards to ensure the quality of the clinical study.
2. The auditor will verify that the eCRF is documented, modified, verified, and processed according to appropriate procedures and that the study is being conducted according to the study plan and objectives.
3. The auditor will confirm that the clinical study is conducted in compliance with the Bioethics and Safety Act, related regulations, and SOPs.
4. The auditor will prepare and review the audit report and submit it to the sponsor. Following the prescribed procedures, the audit report will be finalized, and an audit certificate will be issued.
5. If any violations are identified during the audit, the sponsor will take corrective actions and implement measures to prevent recurrence. If the investigator's continuous violations or serious violations are confirmed, the sponsor may suspend the clinical study participation of the relevant study site.

## Subject Informed Consent

The subject information sheet and informed consent form may be used after approval of the IRB. The investigator must obtain consent for the use of information from the study subjects in accordance with the ethical principles based on the Declaration of Helsinki and the Bioethics and Safety Act standards. The investigator must fully explain the study and obtain written consent from the subjects (or legally acceptable representatives) prior to initiating any study-related procedures. Consent must be obtained in a private setting (e.g., consultation room, examination room). The investigator should retain the original signed consent form in the investigator files, and provide a copy of the signed consent form and information sheet to the subject (or legally acceptable representative).

If the study subject has difficulties in communication due to lack of understanding or ability to express their intentions, written consent must be obtained from the subject’s legal representative. If a subject has no legally acceptable representative, a representative will be appointed in the order of spouse, immediate family, and non-immediate family; if there are more than one immediate or non-immediate family members, it should be decided under an agreement. If an agreement is not reached, the eldest shall be the representative.

Even if the legal representative provides consent, the study subject should also sign and date the consent form, if possible.

If the subject or representative is unable to read, a witness (impartial observer) should be present for the entire consent process. The subject or representative verbally consents to participate in the study, signs the consent form if possible, and the witness signs the form to confirm that the information was accurately conveyed to the subject or representative, that it was understood, and that the consent was given voluntarily.

If there are any changes to the subject information sheet and consent form during the study, re-approval from the IRB must be obtained.

